| Primary endpoint | Fasting glycaemia in prediabetic overweight subjects before and after nutritional intervention |
| Secondary endpoints | To study the influence of 4-month supplementation with Glycabiane on lipid profile (Total cholesterol, LDL-c, HDL-c, TG, etc.), levels of glycosylated haemoglobin, anthropometric characteristics and on the biology of adipose tissue (size of adipocytes, inflammatory status, sensitivity to insulin.  To evaluate safety of 4-month supplementation with Glycabiane  To evaluate quality of life |
| Methodology/Study design | A single centre, randomised, double-blind, placebo-controlled study |
| Criteria for inclusion of subjects | Men and women 25-65 years of age:  - prediabetic: 1.00 g/L ≤ fasting glycaemia < 1.26 g/L,  - overweight or obesity (BMI>25),  - with normal renal and hepatic function tests,  - covered by the French social security system,  - sufficiently cooperative to comply with requirements of the study,  - patients with immunocompetent status (no known HIV or hepatitis C infection),  - use of an effective method of contraception by women of childbearing potential. |
| Criteria for Non-Inclusion of Subjects | - thyroid disorder - hypogonadism - history of a musculo-skeletal, auto-immune or neurological disorder - Hepatitis C, HIV - Medical therapy for thyroid disease, hypoglycaemia or use anti-coagulant therapy - pregnant women or breastfeeding mothers - subject under measure of legal protection - subject who received fees of €4,500 as compensation for participation in clinical trials during the last 12 months. This information is to be verified by the investigator, since subjects are compensated in the study - history of allergy to one of the components of the investigational product - contra-indication to use of xylocaine as a local anaesthetic |
| Number of Patients | 50 subjects: 25 subjects per group |
| Duration of Study | Duration of the inclusion period: 6 months  Duration of participation for each patient: 6 months  Total duration of study: 24 months |
| Expected findings | This first randomised, double-blind, placebo-controlled study of a new combination cinnamon/chromium represents important hope in order to regulate fasting glycaemia in prediabetic overweight subjects with a nutritional product and with a physiological dose in order to limit progression of prediabetes to type 2 diabetes. |

TABLE OF CONTENTS

[I. Study rationale 7](#__RefHeading___Toc394046426)

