## Statement of the experimental design

A population of 60 overweight or obese prediabetic subjects will be selected after an examination for pre-inclusion.

After inclusion, subjects will be randomised to 2 groups to follow 4 month supplementation either with Glycabiane or with Placebo (2 capsules per day). Three follow-up visits will also be scheduled: one after 2 months of supplementation, another at the end of the 4 month supplementation period, and a last one 2 months after the end of supplementation at 6 months.

*Overall study flowchart*

| Visits | V1  Inclusion | V2  D0-Tr | V3  2M | V4  4M  End of tr. | V5  6M  follow-up |
| --- | --- | --- | --- | --- | --- |
| Days | -14 to -1 | 0 | 60±7 | 120±7 | 180±7 |
| Criteria for inclusion/non-inclusion | X | X |  |  |  |
| Invest. Treatment |  | X | x | x |  |
| Information/  Signature of consent form | X | ~~X~~ |  |  |  |
| BP | X | X | X | X | X |
| Weight (kg) | X | X | x | X | x |
| Waistline | X | X | x | x | x |
| **Somatic and nutritional evaluation**  **-** Anthropometric measurements  - Measurements of body composition (DEXA)  - Nutritional diary (see appendix 7) | X  X | x  x  x | x  x | x  x  x | x  x |
| **Screening evaluation:**  -Liver function test evaluations:  AST, ALT, gamma GT  - Renal evaluation: Expanded Ionno  - CBC + platelets  - Serology: HIV, Hepatitis C  - Pregnancy test: Beta-hCG | X |  |  |  |  |
| **Metabolic evaluation**  - Glycaemia  - Serum insulin,  - Lipid evaluation (Cholesterol, LDL-, HDL- Cholesterol, TG)  - Free fatty acids (FFA)  - % HbA1c | x  X | x  x  x  X  x |  | x  x  x  X  x | x  x  x  X  x |
| **Inflammatory evaluation**  - CRPus, IL6 |  | X |  | x | x |
| **Adipose signals**  - Leptine, adiponectin  - Needle puncture of subcutaneous abdominal adipose tissue  - Adipocyte size:  - Study of adipocytes in culture (in vitro) |  | X  x |  | X  x | X |
| **Quality of life questionnaires (TFEQ, physical activity)**  **Dietary questionnaire (diary)** | X | X  X | X | X  X | X  X |

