## Secondary endpoints:

Evaluation of changes in percentage of HbA1c, lipid profile, serum insulin, serum leptin, anthropometric characteristics, adipocyte size at end of supplementation, inflammatory status and sensitivity of adipose tissue to insulin.

Quality of life evaluation

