# Practical conduct of study

## Detailed description of procedures practiced on persons:

So-called screening/inclusion visit D-14 to D-1

- Information of the person who is a subject in the study and collection of his or her consent
- Medical visit and nutritional evaluation
- Laboratory test evaluation specific for inclusion consisting of:
  - complete blood count with white blood cell differential count (CBC-) and erythrocyte sedimentation rate (ESR),
  - HIV and HCV serologies,
  - renal function tests (serum electrolytes (plasma sodium, plasma potassium, calcium, alkaline reserve, serum phosphorus), creatinine, blood urea nitrogen)
  - liver function tests (ALT, AST, Gamma GT)
  - lipid parameter profile (Total cholesterol, HDL and LDL cholesterol, triglycerides)
  - glycaemia
  - a pregnancy test if a female volunteer is not post-menopausal and not using an effective method of contraception
  - nutritional diary (see appendix 7)

Visit V2-D0 -randomisation:

- Verification of criteria for inclusion
- Clinical examination, somatic and nutritional evaluation (blood pressure, weight, waistline, anthropometric measurements including body composition, nutritional diary)
- Laboratory test evaluation after an overnight fast of 8 hours, and including measurement of glycaemia, serum insulin, total cholesterol, LDL-, HDL-, triglycerides, CRPus, IL6, serum leptin, HbA1c
- Needle aspiration of subcutaneous adipose tissue
- Distribution of a nutritional diary and of an operational diary for the next visit
- Distribution and retrieval of quality of life questionnaires TFEQ*, physical activity questionnaires (see appendix 6) and nutritional diary (appendix 7)
- Distribution of treatment (Glycabiane)
- Measurement of body composition (DEXA)
- Setting of an appointment for visit 3 (D60±7)

*The Three Factor Eating Questionnaire (TFEQ) is a self-questionnaire which makes it possible to study three dimensions of dietary behaviour: hunger, restriction and disinhibition. It is defined by occurrence of uncontrolled access of hyperphagia, which most often are subsequent to lifting of dietary restrictions.

Visit 3 (V3 at month 2) at D 60 ± 7

- Clinical examination, somatic and nutritional evaluation (blood pressure, weight, waistline, anthropometric measurements, nutritional diary)
- Recovery of empty boxes and blisters of products consumed
- Setting of an appointment for end of supplementation visit (D120±7)

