Visit 4 (V4 at month 4) at end of supplementation at D 120 ± 7

- Recovery of empty boxes and blisters of products consumed and of remaining products not consumed
- Distribution of nutritional diary and of operating diary for next visit
- Distribution and recovery of quality of life questionnaires, physical activity questionnaire and nutritional diary (appendix 7)
- Clinical examination, somatic and nutritional evaluation (blood pressure, weight, waistline, anthropometric measurements, nutritional diary)
- Laboratory test evaluation after an overnight fast of 8 hours, and including glycaemia, serum insulin, total cholesterol, LDL-, HDL-, triglycerides, CRPus, IL6, serum leptin, HbA1c
- Needle aspiration of subcutaneous adipose tissue
- Measurement of body composition (DEXA)
- Setting of an appointment for the follow-up visit (D194± 7)

Visit 5 (V5-at month 6) of follow-up at D 194 ± 7

- Clinical examination, somatic and nutritional evaluation (blood pressure, weight, waistline, anthropometric measurements, nutritional diary)
- Laboratory test evaluation after an overnight fast of 8 hours, and including glycaemia, serum insulin, total cholesterol, LDL-, HDL-, triglycerides, CRPus, IL6, serum leptin, HbA1c
- Collection of nutritional diary and of operating diary
- Distribution and recovery of quality of life questionnaires
- End of study

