**Secondary analyses**

Other comparisons (secondary evaluation end points) will be:

- levels of HbA1c before and after supplementation. Comparison will be performed within groups and between the two groups.

- concentrations of total cholesterol, HDL-c, LDL-c, TG, ND leptin before and after supplementation. Comparison will be performed within groups and between the two groups

- serum insulin and HOMA before and after supplementation, within groups and between the two groups comparison

- quality of life before and after supplementation

- systemic inflammatory status (IL-6, CRPus)

- adipocyte size before and after supplementation

- inflammatory status of adipose tissue in vitro by ELISA assay measurement (IL-6, adiponectin)

- sensitivity to insulin of adipose tissue in vitro by study of adiponectin secretion and of Akt phosphorylation

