## Appendixe 6: Questionnaires TFEQ et d’activité physique

## Appendixe 7: Carnet alimentaire

## Appendixe 8: Annonce « Métro »

## Appendixe 9: Déclaration d’Helsinki

## Appendixe 10: BPC

## Appendixe 1: Lettre d’information version 1.2

## Appendixe 2: Consentement éclairé version 1.3

## Appendixe 3: Copie de l’attestation d’assurance

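### The quality-of-life endpoint is assigned only an eating-behaviour questionnaire and a physical-activity questionnaire, so it should be renamed for what is measured

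*Protocol*

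**What the plan says.** Quality of life is declared as an outcome in three places of the Protocol. The Synopsis lists it among the secondary endpoints ("To evaluate quality of life"). The section Secondary endpoints repeats it as "Quality of life evaluation", with no instrument, domain or score. The Secondary analyses include "quality of life before and after supplementation".

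The instruments appear elsewhere. The flowchart row reads "Quality of life questionnaires (TFEQ, physical activity". In the Detailed description of procedures, visit V2 has "Distribution and retrieval of quality of life questionnaires TFEQ*, physical activity questionnaires (see appendix 6) and nutritional diary (appendix 7", and the asterisk leads to a note saying that the TFEQ "makes it possible to study three dimensions of dietary behaviour: hunger, restriction and disinhibition". Visit V4 has "Distribution and recovery of quality of life questionnaires, physical activity questionnaire and nutritional diary (appendix 7". Visit V5 mentions quality-of-life questionnaires without naming any. The list of appendices gives "Appendixe 6: Questionnaires TFEQ et d’activité physique".

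The secondary objectives, in both the Synopsis and the Objectives section, do not mention quality of life. They do include dietary intake (Objectives section).

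**The concern.** An endpoint needs an instrument that measures the thing it is named after. Here the name is quality of life, and the main instrument is one that the protocol itself describes as a measure of eating behaviour. If the plan is followed as labelled, a change in restriction, hunger or disinhibition would fall under a quality-of-life heading. A reader could then take it as evidence that the supplement improved or worsened quality of life.

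The direction would be unclear as well. The protocol does not say whether more dietary restriction, or less hunger, counts as better or worse quality of life.

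**Working it through.** No arithmetic applies. The check sets the places that declare the endpoint beside the places that name its instruments.

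1. **Is it a real endpoint or a stray label?** It stands in the Synopsis, in the section Secondary endpoints and in the Secondary analyses. It is a declared endpoint with a planned analysis.

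2. **Which instruments are attached to it?** The flowchart and visit V2 give two: the TFEQ and a physical-activity questionnaire. The title of Appendix 6 names the same two. No generic or disease-specific quality-of-life scale appears anywhere in the Protocol.

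3. **What does each instrument measure?**
   - TFEQ: by the protocol's own note, three aspects of eating behaviour. This follows directly from the text.
   - Physical-activity questionnaire: activity, by its title. Its items are not shown, so this half rests on the title alone.

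4. **Do the visit texts change the picture?** At V4 the activity questionnaire is listed separately, after the quality-of-life questionnaires. On that reading the TFEQ alone carries the endpoint. On the flowchart's reading both do. Under either reading, no named instrument is described as measuring quality of life.

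5. **Could a statistical analysis plan repair it?** Such a plan can define scores, models and populations. It cannot create data on something that was not asked of the subjects. The fault lies in the pairing of endpoint name and instrument, which the Protocol fixes.

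6. **What depends on it?** The primary endpoint is fasting glycaemia. The sample size rests on a 10% difference in that variable, a standard deviation of 0.13 g/L, an alpha of 0.05 and 90% power. None of these involves the questionnaires.

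**The case against.** The fair case on the other side has several parts.

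- *The labelling is transparent.* The flowchart puts the instruments in brackets beside the label and V2 explains the TFEQ, so an attentive reader can tell what the scores are. The Synopsis row on expected findings makes no quality-of-life claim. This stands as a limit on the harm: a misleading report is a risk, not something the protocol announces. It does not remove the mismatch, because the endpoint and analysis sections use the label without naming the instruments.

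- *The activity questionnaire cannot be inspected.* This also stands. That instrument is known only by its title, so the statement that it does not measure quality of life is less secure than the one about the TFEQ.

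- *The change is not purely editorial.* The section Substantial changes to the protocol requires every change to be classified, and a substantial one needs a favourable ethics committee opinion. This stands and belongs in the cost.

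Two stronger readings are tempting, and the document supports neither.

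- A reader might infer that quality of life is singled out because its analysis line has no between-group comparison, unlike the lines for HbA1c, lipids and HOMA. But the lines for systemic inflammation, adipocyte size and the in vitro adipose measures also lack that wording. The Statistical considerations provide descriptive statistics by group and repeated-measures analysis of variance for quantitative data. The detail may properly be left to a statistical analysis plan.

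- A reader might infer that diverging diet or activity would threaten the primary comparison. The trial is randomised, double-blind and placebo-controlled. A difference in behaviour that arises after randomisation may be chance or part of the product's effect, and does not in itself bias the comparison of fasting glycaemia. Behaviour is also already addressed, through the inclusion criterion on unchanged habits, the instruction not to alter diet, and the diaries.

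**Conclusion.** The point holds as a mismatch between an endpoint's name and its measure. As written, the trial can report eating behaviour and physical activity but cannot support a conclusion about quality of life.

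The severity is minor. One secondary endpoint is affected and no figure in the plan changes. For the TFEQ the conclusion rests on the protocol's own definition. For the other questionnaire it assumes that the content matches the title. It also assumes that no further questionnaire is administered beyond those named.

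**What to change.** Rename the endpoint *eating behaviour (TFEQ restriction, disinhibition and hunger scores) and physical activity* in the Synopsis, the flowchart, the section Secondary endpoints, the descriptions of visits V2, V4 and V5, and the Secondary analyses. Report each score under its own name and draw no quality-of-life conclusion. The scores may be shown by group beside diary intake as descriptive context for the glycaemia result. They should not be used to adjust the primary test.

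The cost is wording, plus classification of the change under the section Substantial changes to the protocol and, if it is judged substantial, an ethics committee opinion. No new visit, sample or questionnaire is needed. The downside is that one advertised endpoint is given up. A sponsor that wants to keep it would have to add a validated quality-of-life instrument at the questionnaire visits V2, V4 and V5, which is a larger change.

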# Evaluation endpoints

## Primary endpoint

Quantification of improvement in fasting glycaemia.

## Secondary endpoints:

Evaluation of changes in percentage of HbA1c, lipid profile, serum insulin, serum leptin, anthropometric characteristics, adipocyte size at end of supplementation, inflammatory status and sensitivity of adipose tissue to insulin.

Quality of life evaluation

# Screening of persons

## Participating studied population:

### Duration of participation of persons in the study:

Total duration of participation of each subject will be 6 consecutive months.

### Description of participating persons:

Criteria for inclusion

- Men and women 25 to 65 years of age,

- Who satisfy the following criteria:

- 1.0 g/L ≤ fasting glycaemia < 1.26 g/L

- Overweight or obese (BMI ≥ 25)

- Who do not wish to change their dietary habits and physical activity,

- With normal renal and liver function test evaluations,

- Covered by the French social security system,

- Sufficiently cooperative to comply with requirements of the study,

- Immunocompetent status (no known HIV nor hepatitis C virus),

- Use of an effective method of contraception for women of childbearing potential

Criteria for exclusion

- thyroid disease
- hypogonadism

- history of a musculo-skeletal, auto-immune or neurological disorder

- hepatitis C, HIV

- medical therapy for thyroid disease, hypoglycaemia or anti-coagulant therapy

- medical therapy than can have an influence on:

- weight gain/loss

- glycaemic control

- serum insulin

- pregnant women or nursing mother

- weight loss > 5% during last 6 months

- ingestion of a dietary supplement containing cinnamon or chromium

- subject who is under legal protection,
- subject who collected €4,500 as compensation for participating in clinical trials during the last 12 months. This information is to be verified by the investigator, subjects are compensated in research studies
- history of allergy to one of the components of the investigational product
- contra-indication to use of xylocaine as a local anaesthetic

### Number of persons to include:

Calculation of sample size: 25 subjects per group are necessary to demonstrate a change in fasting glycaemia of at least 10% and of a standard deviation 0.13 g/L (mean of standard deviations observed in clinical studies published on type 2 diabetes and cinnamon), setting an risk of 0.05 and a  risk of 0.10. 60 subjects will be selected in the study according to criteria for inclusion and non-inclusion to ensure inclusion and follow-up of the study for 50 subjects in its totality.

## Recruitment and withdrawals from study

### Recruitment

Subjects will be recruited by different methods of a communication campaign displayed:

- in medical offices of doctors practicing in Paris or in the Paris area, via posters printed by the CRNH (see appendix 8)
- doctors who wish to do so may also offer the study to patients during a consultation. Their contribution to the study will be limited to pre-screening of overweight and or obese prediabetic patients based on voluntary participation of subjects with an abnormal glycaemia (1.0 g/L ≥ fasting glycaemia > 1.26 g/L), satisfying screening criteria, who read the information sheet and accept to come to the department of Nutrition of Pitié Salpêtrière hospital group to validate their inclusion in this study or not.
- in biomedical clinical analyses laboratories, pharmacies, centres of screening for diabetes via posters printed by the CRNH (see appendix 8)
- in the daily newspaper “Métro”, Paris edition (see copy of poster in appendix 8)
- via “Volterys”, a “meeting site” for volunteer subjects and researchers

Subjects will be selected based on medical interview, a complete clinical examination performed by the investigator or co-investigator and laboratory test evaluation.

### Withdrawals from study

**Criteria for discontinuation or withdrawal from study:**

- a serious adverse event, that is “any event or adverse effect which results in death, is life-threatening for the person who is the subject in the research, requires hospitalisation or results in prolongation of hospitalisation, causes incapacity or major or durable disability or in fact is translated by a congenital anomaly or malformation, whatever the dose administered” (ICH E6: GCP, 1.50).
- non-compliance with the study protocol.

**Deliberate decision of a person:**

Withdrawal from the study is possible at any time if requested by the participant. In particular, if participants do not wish to continue tests, it is sufficient for them to notify this to the examiner.

**An imposed decision**:

Participants who cannot execute tasks relating to the study will be excluded from the study.

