## Provisional study schedule (Flow-Chart)

- Duration of inclusion period: 6 months

In case of withdrawals from study for medical intercurrent reason, subject withdrawn will not replaced

- Total study duration: 24 months
- Total duration of participation of each subject will be 194 consecutive days.

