# Collection of human biological samples

- Description of type of samples:

Blood samples and adipose tissue.

- Description of conditions for sampling:

Blood samples will be collected at D-1 to -14, D0, D 120 and D180 after 8 hours of fasting, between 8 and 9:30 am. Test tubes collected will be kept at 4 °C starting with collection of the sample, centrifuged to 4 °C, divided into aliquots and stored at -80 °C until their use for the planned analyses.

The sample of adipose tissue will be collected after application of local anaesthesia with 2 ml of 1% xylocaine without isoprenaline, peri-umbilical adipose tissue sample will be collected by suctioning with a fine needle to measure the adipocyte size immediately and to conduct study of cell culture in vitro.

Blood samples will be stored by INSERM U872 (Eq7) at -80 °C up until end of study (last analysis of last patient included), and then they will be destroyed. Those of peri-umbilical adipose tissue will be stored at -80 °C by ADIPOPHYT up until end of study (last analysis of last patient included), and then they will be destroyed.

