**Primary analysis**

The primary evaluation end point will be the fasting glycaemia before and after supplementation. It will be compared within groups and between the two groups using a test of comparison of means.

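### The withdrawal rules do not separate stopping the product from leaving follow-up, so a randomised subject removed before D120 has no end-of-supplementation fasting glycaemia

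*Protocol*

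**What the plan says.** Section VI.B.2 (Withdrawals from study) has a list headed "Criteria for discontinuation or withdrawal from study". It contains two entries: a serious adverse event, and "non-compliance with the study protocol". Under the imposed decision in the same section: "Participants who cannot execute tasks relating to the study will be excluded from the study". Withdrawal at the participant's own request is dealt with separately.

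Subjects are randomised at V2, on D0 (section VII.A), so these rules apply to randomised subjects. On sampling, section X says: "Blood samples will be collected at D-1 to -14, D0, D 120 and D180 after 8 hours of fasting". On the primary analysis, section XIII says: "The primary evaluation end point will be the fasting glycaemia before and after supplementation". It is to be compared within and between groups by a comparison of means. For subjects who leave early, section XIII provides a frequency table and a listing of reasons.

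**The concern.** All the listed grounds arise after randomisation. If meeting one of them ends participation rather than only product intake, the subject's D120 glycaemia is not collected. The comparison then rests on those who stayed, and randomisation no longer guarantees that the two remaining groups are alike.

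The link to outcome is plausible. Section VIII.B authorises no treatment acting on glycaemic control during the trial, and section IX tells subjects not to change their diet. A subject who starts such a treatment or changes diet has departed from the protocol and could be withdrawn for it. If this, or intolerance of the product, differs between arms, the missing values are not a random subset. The loss arises from what the protocol collects, so it cannot be repaired at the analysis stage.

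**Working it through.** The protocol gives no figure on this point (no removal rate, no bias estimate), so there is none to reproduce. The main check sets the sections side by side.

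**1. When the primary variable is measured** (flowchart in IV.C, visit descriptions in VII.A, sampling in X)

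| Visit | Fasting glycaemia |
|---|---|
| V1, D-14 to D-1 | yes (screening) |
| V2, D0, randomisation | yes (baseline) |
| V3, D60 | no |
| V4, D120, end of supplementation | yes |
| V5, follow-up (D180 in IV.C and X, D194 in VII.A) | yes, off product |

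A subject who leaves between D0 and D120 has no post-baseline value. One who leaves after D120 keeps the primary value.

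**2. Whether each ground costs the D120 value**

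- *Unable to execute tasks.* The text says excluded from the study. The value is lost if this happens before D120.
- *Serious adverse event.* The heading covers discontinuation or withdrawal and could partly mean stopping the product. Sections XI.B and XI.D keep medical follow-up after such an event but name no glycaemia sample. The value may be lost.
- *Non-compliance.* Section VIII.B assesses compliance by interview and by return of unused product. V3 recovers only empty boxes and blisters; unconsumed product comes back at V4, when the fasting sample is taken. Non-compliance first found there costs nothing. If it is found earlier, by interview or at V3, or is another kind of protocol breach, the value may be lost.

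**3. Whether any section retains removed subjects for D120.** None does.

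**4. Illustration of the mechanism only, on assumptions that are not in the protocol.** Assume no true effect, 30 per arm, normal outcomes with the SD of 0.13 g/L from section VI.A.3, and equal numbers removed in each arm: at random on placebo, and on active those with the highest removal score, where the score has correlation r with the outcome. In large samples, with a fraction f removed, z the (1 - f) normal quantile and φ the normal density,

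bias = -r × 0.13 × φ(z) / (1 - f).

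- 3 of 30 removed (f = 0.10): φ(z)/(1 - f) = 0.1755/0.90 = 0.195, so bias = -0.0254 × r.
- 8 of 30 removed (f = 0.267): φ(z)/(1 - f) = 0.3286/0.7333 = 0.448, so bias = -0.0583 × r.

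Simulation (40,000 runs, two-sided 5% t-test):

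| Removed per arm | r | Bias (g/L) | Type I error, remaining subjects |
|---|---|---|---|
| 3 of 30 | 0.3 | -0.0075 | 5.5% |
| 3 of 30 | 0.5 | -0.0119 | 6.6% |
| 3 of 30 | 1.0 | -0.0243 | 12.8% |
| 8 of 30 | 0.3 | -0.0169 | 7.5% |
| 8 of 30 | 0.5 | -0.0281 | 11.8% |
| 8 of 30 | 1.0 | -0.0569 | 37.9% |

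With everyone measured, type I error is 4.8% to 5.1%. The rows with r = 1.0 are an extreme bound. Removing the lowest scores on active instead reverses the sign. The table shows that the effect can range from trivial to serious; it is not an estimate for this trial.

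**The case against.** The strongest reply is that little primary data may be lost. Unused capsules return at V4 alongside the fasting sample, so much capsule non-compliance would surface too late to cost the value. Serious adverse events are expected to be rare for this product (sections I.D and XI.E). Some subjects who cannot do study tasks could not attend V4 under any rule. The prohibited-treatment route is also weaker than it looks. The trial takes no glycaemia between D0 and D120, so a rise would have to be found elsewhere, and section IX only requires new therapy to be reported. Removal would follow only if this were classed as non-compliance. Blinding further limits differences by arm. All of this stands, and it bears on how much is lost.

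A reader might go further and infer that the protocol plans a completer analysis. The document does not support that. The primary analysis names no population, and the choice of analysis set may properly sit in a statistical analysis plan that is not shown. The sample-size wording, "to ensure inclusion and follow-up of the study for 50 subjects in its totality", reads as an allowance for losses and defines no analysis set.

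A reader might also take the gap between 60 and 50 as the expected loss after randomisation. Section XIII says 60 are screened and section VI.A.3 says 60 are selected, in each case to secure inclusion as well as follow-up of 50. The ten may therefore include subjects lost before randomisation.

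What the reply does not answer is that no section keeps a removed subject for D120. An analysis plan can name an intention-to-treat set and impute, but it cannot supply a sample that was not taken.

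**Conclusion.** The point holds in a limited form. The exclusion of subjects who cannot do study tasks is explicit. The list covering non-compliance and serious adverse events is loosely worded and does not say whether follow-up ends. Under either rule, a randomised subject removed before D120 has no end-of-supplementation primary value, and if removal depends on arm and outcome the between-group comparison is biased in an unknown direction.

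The size cannot be estimated from the documents: they give no removal rate, none by arm, and nothing on the link between removal and glycaemia. The conclusion rests on two readings: that leaving the study means no V4 sample, and that at least some removals would occur before D120. It does not extend to non-compliance first detected at V4, nor to subjects removed after D120. The change is worth making because the loss would be irrecoverable and preventing it costs little.

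**What to change.** In section VI.B.2, separate stopping the product from leaving follow-up. Leave the clinical rules on who stops the product unchanged. Reword the withdrawal list and the imposed-decision paragraph so that stopping the product, non-compliance, or inability to do some study tasks does not by itself end follow-up. Add to section VII.A that every randomised subject who has not withdrawn consent and is able to attend is asked to give the V4 (D120) fasting sample, whether or not still taking product. State in section XIII that these values enter the primary between-group comparison by randomised arm.

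The cost is a protocol wording change and a few V4 visits, already in the schedule, kept for subjects off product. The downside is a slightly diluted estimate, since some subjects measured at D120 will not have taken the full course.
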